#### Sampling

To collect the quantitative data, the researcher would refer to the obstetrics clinic of the Taleghani hospital and would choose the eligible women referring to this clinic through a convenient sampling method. Then, a comprehensive description of the study will be given to the women about the research, its goals, and its methodology, and if they were willing to participate, a written informed consent form would be signed. Next, questionnaires would be completed about the socio-demographic and obstetrical history followed by filling up the Edinburgh’s Postpartum Depression Scale (EPDS) via interview. Note that pregnant women with a depression score of less than 13 will be included.

#### Randomization and allocation concealment

To allocate the participants to the studied groups, a randomized block method with 4- and 6-blocks will be used with an allocation ratio of 1:1. For allocation concealment, the type of intervention is written in a piece of paper and will be placed inside consecutively numbered opaque envelopes. Random allocation and allocation concealment will be conducted by a person not involving in the sampling and data collection. After the study participants signed the consent form, the relevant envelope will be opened, and the intervention will be implemented.

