#### Intervention and follow-up

After allocating the participants in this study groups, for those in the intervention group, an educational session will be held to explain the birth plan, whereby all items of the birth plan will be explained. Also, an educational pamphlet in which all items of the birth plan checklist are explained will be provided to the participants of the intervention group. During the session, the researcher’s phone number will be provided to the mothers, and she will answer any questions of participants about the birth plan. In the case of the mother’s preparation, the mother-requested birth plan will be developed by the researcher in the very first session. If the mothers are not prepared, however, the next session will be set up with the participant to develop the birth plan. The established birth plan will be confirmed by an Obstetrician. Within the interval between the in-person session and time of delivery, the researcher will be in contact with mothers through phone, or in case the mother wished, will contact in person. Also, the participant will be asked to contact the researcher as soon as they referred to the hospital. With the entrance of the participants to the labor ward of the hospital, the birth plan will be implemented by the researcher. Also, the participants in the study groups will receive routine and standard care. Immediately during and after delivery, the delivery information questionnaire, neonatal information, and Delivery Fear Scale (DFS) will be completed. Also, a partogram will be completed by the researcher for all participants. The participants in both groups will be followed-up for 6 weeks postpartum. The childbirth experience questionnaire-2 (CEQ 2.0), EPDS, and PTSD Symptom Scale 1 (PSS-I) will be completed 6 weeks after delivery in Taleghani Hospital by the researcher through interviews.

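### The researcher who picks women by convenience also knows past allocations, so blocks of 4 and 6 leave up to about 69% of assignments guessable: a selection-bias risk of uncertain size

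*Protocol article*

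**What the plan says.** Under Randomization and allocation concealment, "a randomized block method with 4- and 6-blocks will be used with an allocation ratio of 1:1". The slips "will be placed inside consecutively numbered opaque envelopes", and "Random allocation and allocation concealment will be conducted by a person not involving in the sampling and data collection". The envelope is opened after consent.

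Under Sampling, the researcher goes to the clinic and "would choose the eligible women referring to this clinic through a convenient sampling method".

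Under Intervention and follow-up, the same role has three further tasks:

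- If the woman is ready, "the mother-requested birth plan will be developed by the researcher in the very first session".
- In labour, "the birth plan will be implemented by the researcher".
- In both arms, "a partogram will be completed by the researcher for all participants". The researcher also conducts the six-week interviews.

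No stratification and no blinding are described, and there is one hospital.

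**The concern.** Concealment has two parts. The next slip must be hidden, and the recruiter must not be able to work it out from earlier slips. The envelopes and the independent person deal with the first part. The second is open here, because the person who decides whom to approach delivers the intervention and so knows who received it. Permuted blocks bring the arms back to equality every 4 or 6 women, so the arm that is behind is the better bet.

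Prediction does harm only if the recruiter can act on it. Convenience choice sets no order of approach, so a particular woman can be invited now or later. Some entry criteria, such as willingness to deliver vaginally, also involve judgement. If women who look likely to have a shorter labour or a better experience were steered towards one arm, even unconsciously, both main outcomes (childbirth experience and active-phase duration) would shift for reasons unrelated to the birth plan.

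**Working it through.** **1. The plan's own benchmark (Sample size).** The active-phase means are 276.7 and 221.4 min, so the planned effect is 55.3 min, with SD 91.3, α = 0.05 and power 90%. The one-sided normal formula gives n = 2 × (1.645 + 1.282)² × (91.3/55.3)² = 46.7, so 47 per arm. The t distribution gives 48, the plan's figure (a two-sided test would need 58 or 59). Then 48 × 1.10 = 52.8, so 53 per arm and 106 in total. The plan gives no figure for predictability, so what follows is this review's own calculation.

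**2. Guessability.** Take a guesser who always bets on the arm behind and tosses a coin at ties. The expected number of correct guesses in a block of 2m is m + ½ × (4^m / C(2m, m) − 1).

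- Block of 4: 2 + ½ × (16/6 − 1) = 2.833, and 2.833/4 = 70.8%.
- Block of 6: 3 + ½ × (64/20 − 1) = 4.1, and 4.1/6 = 68.3%.
- Equal numbers of both: (2.833 + 4.1)/10 = 69.3%.

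A simulation of 20,000 lists of 106, with block sizes drawn at random and unknown to the guesser, gives 69.2% (95% of lists between 66.5% and 71.7%). That is about 20 correct guesses more than the 53 expected by chance. An imbalance points to an arm at about 61% of positions, and the guess is right about 81% of the time there. The rule needs no knowledge of block sizes, so mixing or withholding them does not lower the figure.

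**3. From guess to shift.** Assume two kinds of women who differ in prognosis by a stated gap, and let the recruiter favour one kind according to the guess. With a 75:25 preference, s = 0.75 − 0.25 = 0.50. With 62.5:37.5, s = 0.25. The arms then differ in case mix by s × (2G − 1), where G is the share guessed correctly. With G = 0.69, 2G − 1 = 0.38. Neither the gaps nor the preferences come from the protocol.

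| Gap | Preference | Shift in active phase | Share of 55.3 min |
|---|---|---|---|
| 1 SD (91.3 min) | 75:25 | 0.50 × 0.38 × 91.3 = 17.3 min | 31% |
| 1 SD | 62.5:37.5 | 0.25 × 0.38 × 91.3 = 8.7 min | 16% |
| 0.3 SD (27.4 min) | 75:25 | 0.50 × 0.38 × 27.4 = 5.2 min | 9% |
| 0.3 SD | 62.5:37.5 | 0.25 × 0.38 × 27.4 = 2.6 min | 5% |

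In SD units the extremes are 0.25 × 0.38 × 0.3 = 0.03 and 0.50 × 0.38 = 0.19. If the same gaps applied to childbirth experience (SD 0.73, planned difference 3.25 − 2.71 = 0.54), the shift would be 0.0285 × 0.73 = 0.02 to 0.19 × 0.73 = 0.14 points, or 4% to 26% of the planned difference.

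If there were no true effect and the shift favoured the birth plan, one-sided type I error would be 1 − Φ(1.645 − shift/√(2/53)), with √(2/53) = 0.194. That is about 7% at 0.03 SD and about 25% at 0.19 SD, against the nominal 5%. All these figures are before covariate adjustment.

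**4. A less predictable list.** A big stick list tosses a fair coin unless the arms already differ by a limit, and then forces the lagging arm. With limit 4 the long-run share of time at the limit is 2/16 = 12.5%, so guessing succeeds 50% + 6.25% = 56% of the time. Simulated lists of 106 give 55.9%, with 11.7% of assignments forced. With G = 0.56, 2G − 1 = 0.12, and the worst case in the table falls to 0.50 × 0.12 × 91.3 = 5.5 min (10%). Under the present blocks, a guesser who knows the possible sizes is certain of 5.7% of assignments.

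**The case against.** The scheme is coherent as written: mixed block sizes, an independent allocator, numbered opaque envelopes and opening after consent. Nothing in it is misstated. The 69% is a ceiling, reached only by someone who tracks all 106 allocations and always bets on the lagging arm. At about 39% of positions the arms are level and that rule has only a coin toss.

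The largest shift needs a full SD between kinds of women and a 75:25 preference at every enrolment. Number of deliveries is recorded, and the Data analysis section adjusts for socio-demographic, obstetric and delivery characteristics. Depression and fear of childbirth are also measured in pregnancy. What is left is motivation and cooperativeness, and nothing in the protocol suggests that these move active-phase duration by 1 SD. Some links are also inferred: the protocol does not call the trial open or unstratified, and it speaks of the researcher as one role without stating that one person fills it throughout.

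Most of this stands, and it limits the size of the concern. It does not remove the mechanism. A person who delivers the intervention cannot be unaware of it, and the envelopes do not hide the past. Adjustment reaches only what is recorded, and the questionnaires as described name no measure of motivation or cooperativeness.

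**Conclusion.** The plan lets a recruiter who knows past allocations choose whom to approach, under a list of which up to about 69% could be guessed. That is a real and avoidable risk of selection bias. A plausible range is about 3 to 17 min of active phase (5% to 31% of the planned effect) before adjustment, entirely conditional on the assumed gaps and preferences.

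A reader might infer that the comparison will be biased, or that a 31% distortion is to be expected. The protocol supports neither. It does not show that anyone will track allocations or select on them, and part of the worst case, such as a difference in parity, could be removed by the planned adjustment. Nor is the envelope procedure itself faulty. The point is a cheap improvement to the design and does not invalidate it.

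**What to change.** **Main change.** In Sampling, replace convenience choice with an invitation to every consecutive eligible attender in the researcher's clinic sessions, with a log of women eligible, invited and refusing. State in the randomization section that eligibility and baseline data, including the EPDS, are complete before the envelope is opened. Sampling places the EPDS after consent and makes it decide inclusion, while the randomization section opens the envelope after consent without giving the order. The cost is two reworded sentences and a simple log. Sample size does not change.

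**Optional second change.** Have the same independent person generate a less predictable list, for example big stick with limit 4, with the limit not disclosed to the recruiter. Guessability falls to about 56%. There are two costs. The final arms may differ by up to 4 women: 51 and 55 give an effective 2 × 51 × 55/106 = 52.9 per arm instead of 53. About 12% of assignments are forced, and these become predictable if the limit is known or worked out, against about 6% certain ones now. If consecutive invitation is followed strictly, this second step adds less, because the recruiter has little room to act on a guess.

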#### Intervention and follow-up

After allocating the participants in this study groups, for those in the intervention group, an educational session will be held to explain the birth plan, whereby all items of the birth plan will be explained. Also, an educational pamphlet in which all items of the birth plan checklist are explained will be provided to the participants of the intervention group. During the session, the researcher’s phone number will be provided to the mothers, and she will answer any questions of participants about the birth plan. In the case of the mother’s preparation, the mother-requested birth plan will be developed by the researcher in the very first session. If the mothers are not prepared, however, the next session will be set up with the participant to develop the birth plan. The established birth plan will be confirmed by an Obstetrician. Within the interval between the in-person session and time of delivery, the researcher will be in contact with mothers through phone, or in case the mother wished, will contact in person. Also, the participant will be asked to contact the researcher as soon as they referred to the hospital. With the entrance of the participants to the labor ward of the hospital, the birth plan will be implemented by the researcher. Also, the participants in the study groups will receive routine and standard care. Immediately during and after delivery, the delivery information questionnaire, neonatal information, and Delivery Fear Scale (DFS) will be completed. Also, a partogram will be completed by the researcher for all participants. The participants in both groups will be followed-up for 6 weeks postpartum. The childbirth experience questionnaire-2 (CEQ 2.0), EPDS, and PTSD Symptom Scale 1 (PSS-I) will be completed 6 weeks after delivery in Taleghani Hospital by the researcher through interviews.

### Quantitative study

#### Scales and data collection

To collect quantitative data, socio-demographic as well as obstetrics history, birth plan checklist, Childbirth Experience Questionnaire (CEQ 2.0), Edinburgh’s Postpartum Depression Scale (EPDS), partogram, Delivery Fear Scale (DFS), PTSD Symptom Scale 1 (PSS-I), and a checklist of maternal as well as neonatal outcomes will be used, and the information will be collected through face-to-face interview method.

##### Socio-demographic and obstetric characteristics questionnaires

This questionnaire will contain items about age, level of education, occupation, having companion, religion, ethnicity, marital status, residence status, household income, being rural or urban, etc. The obstetric questionnaire has items about the number of pregnancies, number of deliveries, number of abortions, history of infertility, etc.

##### Childbirth experience questionnaire (CEQ 2.0)

This instrument contained 25 items and measures the childbirth experience for women. The questionnaire covers the following areas: personal capacity (locus of control is a psychological concept that refers to how strongly people believe they have control over the situations and experiences that affect their lives.], personal feelings about childbirth and labor pain), professional support (midwifery care and information), perceived security (sense of security and memories of childbirth), and participation (the person’s ability to change the position, movements, and pain mitigation during labor). Specifically, 23 items are multiple-choice (with four options), and three items are completed based on a visual analog scale (VAS). The responses are in the form of absolutely agree (score 1), often agree (score 2), often disagree (score 3), and absolutely disagree (score 4). The items responded based on VAS will be changed into values 1–4: scores 0–40 (score 1), scores 41–60 (score 2), scores 61–80 (score 3), and scores (81–100) (score 4). Sentences with negative concepts (experience of severe pain, sense of fatigue, fear, and having bad memory) are scored negatively. High mean values in this instrument represent a more positive childbirth experience [22]. Also, the reliability and validity of the Persian version of this questionnaire have been determined in the research setting by Ghanbari Homaei et al. [23]. Where the Cronbach alpha coefficient of items and the intra-class correlation coefficient was reported to be 0.93 and 0.97, respectively [23], this instrument will be completed 6 weeks postpartum via interview.

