#### Sample size

The sample size in this study was calculated based on the two variables of “childbirth experience” and “duration of the active phase of labor” using G-power software. Based on the results of the study by Ghanbari Homaei et al. [21] on the variables of childbirth experience and considering m_1_ = 2.71, m_2_ = 3.25 (assuming 20% increase in response to the intervention), sd_1_ = sd_2_ = 0.73, one-sided α = 0.05, and power = 90%, the sample size was calculated 32 participants; considering 10% attrition, the sample size will be 35 in each group. According to the variable of the duration of the active phase of labor and concerning m_1_ = 276.7, m_2_ = 221.4 (assuming 20% reduction in response to intervention), sd_1_ = sd_2_ = 91.3, α = 0.05, and power = 90%, it was calculated as 48 participants, and eventually, it will be 53 as the sample size in each group, given 10% possible attrition. Since the sample size calculated based on the variable of the duration of the active phase of labor would be more extensive. Thus the final sample size was considered 53 in each group.

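### The printed CEQ 2.0 response key contradicts the score direction stated for this lead outcome and the increase planned for it, and the item count does not add up

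*Protocol article*

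**What the plan says.** The section on the Childbirth experience questionnaire (CEQ 2.0) gives these scoring statements:

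- Multiple-choice responses are coded "absolutely agree (score 1), often agree (score 2), often disagree (score 3), and absolutely disagree (score 4".
- Visual analogue responses are banded upward: "scores 0–40 (score 1), scores 41–60 (score 2), scores 61–80 (score 3), and scores (81–100) (score 4".
- One group of items is treated differently: "Sentences with negative concepts (experience of severe pain, sense of fatigue, fear, and having bad memory) are scored negatively".
- The direction of the total is given as "High mean values in this instrument represent a more positive childbirth experience".
- On the number of items, it says "This instrument contained 25 items" and then "23 items are multiple-choice (with four options), and three items are completed based on a visual analog scale".

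Comparing mean childbirth experience between groups is the first specific objective of the quantitative phase. The Sample size section plans a change in this score from 2.71 to 3.25, "assuming 20% increase in response to the intervention", with SD 0.73, one-sided α = 0.05 and 90% power.

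**The concern.** A score on which higher is better needs agreement with a favourable statement to earn a high mark. The printed key gives it the lowest mark. The only reversal mentioned is for unfavourable statements, so nothing in the text turns the favourable ones round. The stated direction and the planned increase therefore conflict with the item coding in the same article.

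The sign of the treatment effect on a lead outcome is at stake. Anyone who wrote scoring syntax from this paragraph, or re-analysed the data with it, could produce a total on which better experiences score lower and read it as the text instructs. The mismatch in the item count adds a smaller doubt about what the mean is taken over.

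**Working it through.** **Planned direction.** From the Sample size section, 2.71 × 1.20 = 3.252, so the planned difference is 3.25 − 2.71 = +0.54. The stated size reproduces: n = 2 × (1.645 + 1.282)² × 0.73² / 0.54² = 31.3, rounded up to the stated 32 per group. The planning figures thus treat benefit as an increase.

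**Item direction under the printed key.** "Scored negatively" can be read in two ways.

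- *Reading A, the ordinary sense: negative sentences are reversed from the listed code.* Agreeing with a favourable sentence scores 1. Disagreeing with a negative one scores 4 on the list and 1 after reversal. Every multiple-choice item then runs low = good, however many are negative.
- *Reading B: negative sentences keep the listed code, so disagreement scores 4.* Those items run high = good, but the favourable ones still run low = good.

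Neither reading makes favourable items run high = good.

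**Illustrative totals, reading A.** The article does not give the analogue anchors or a split of items that sums to 25. Assume that 100 is favourable after any reversal, so the best response scores 4, and take three possible splits:

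| Multiple-choice + analogue | Best experience | Worst experience |
|---|---|---|
| 22 + 3 | (22×1 + 3×4)/25 = 1.36 | (22×4 + 3×1)/25 = 3.64 |
| 23 + 3 | (23×1 + 3×4)/26 = 1.35 | (23×4 + 3×1)/26 = 3.65 |
| 23 + 2 | (23×1 + 2×4)/25 = 1.24 | (23×4 + 2×1)/25 = 3.76 |

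If 100 is instead the unfavourable end and is not reversed, the analogue items also run low = good. The total is then fully inverted, with best 1.00 and worst 4.00. With every item running high = positive, the best is 4.00 and the worst 1.00.

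**Illustrative totals, reading B.** With k negative items and a 22 + 3 split, the best is (34 + 3k)/25 and the worst is (91 − 3k)/25. The article lists four negative concepts; if these meant four items, the best would be 46/25 = 1.84 and the worst 79/25 = 3.16. The two are equal at k = 9.5 (at 10 for 23 + 3, and at 10.5 for 23 + 2). Below that number the total is inverted; near it, the total hardly separates good from bad experiences; above it, the total runs in the stated direction while the favourable items still pull against it.

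**What the planned effect would look like.** Reversing a 1–4 item turns x into 5 − x. Under reading A, and taking the planned means to apply to every item, multiple-choice means of 2.71 and 3.25 become 2.29 and 1.75. With 22 + 3 items the totals are (22×2.29 + 3×2.71)/25 = 2.34 and (22×1.75 + 3×3.25)/25 = 1.93. The planned +0.54 is then recorded as about −0.41.

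**Item count.** 23 + 3 = 26, not 25.

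**The case against.** The strongest reply is that this is a misprinted key in a condensed article. The same paragraph states the intended direction, the planning means agree with it, and the instrument is an existing questionnaire whose Persian version is said to have been validated in the same setting. A team scoring from that form would get the right sign. This is plausible and it limits the consequence: the inversion arises only if the key is applied as printed. It does not remove the contradiction, because the printed key is the only scoring rule the article gives.

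Three stronger readings are tempting, and the document does not support them.

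- A reader might infer that the analogue items certainly run against the multiple-choice items. The anchors are not given, and neither are the items that use the analogue format. Severe pain appears only in the list of negative sentences, so treating it as an analogue item would be a guess. The contradiction in the multiple-choice key does not need this argument.
- A reader might infer that the planned test for an increase is bound to fail. One-sided α appears only in the Sample size section. The Data analysis section names one-way analysis of variance and regression, which are not described as directional.
- A reader might infer that the mean has no defined denominator. The administered form fixes the number of items, so 25 against 26 is a counting error to correct and not a missing definition.

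**Conclusion.** The scoring text is wrong as written. Coding agreement as 1 and reversing only negative sentences cannot be reconciled with a high-is-positive score, or with a benefit planned as a rise from 2.71 to 3.25. This follows from the article alone and holds under both readings of the reversal rule.

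The size of the consequence is conditional. If the scale is scored as printed, a true benefit would tend to appear as a lower score. Under the ordinary reading of the reversal, with favourable analogue anchors and 22–23 multiple-choice plus 2–3 analogue items, the best experience averages about 1.24 to 1.36 and the worst about 3.64 to 3.76. The item splits and anchors are assumptions, so these figures are illustrations. The document does not show that the trial's data will be scored this way, nor that its result will have the wrong sign. The item count is a separate, minor inconsistency. The sample size is unaffected, because its inputs already assume that higher is better.

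**What to change.** First check the paragraph against the validated Persian form. Then:

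1. Restate the key so that every item runs high = positive: favourable items from absolutely agree = 4 to absolutely disagree = 1, with negatively worded items reversed and identified by number.
2. State the anchors of the visual analogue items and which of them, if any, are reversed before banding.
3. Correct the item count so that the two formats sum to the stated total, and use that number for the mean.
4. Test the scoring syntax on a constructed best and worst response pattern, which should return 4.00 and 1.00.

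The cost is one paragraph of text and the scoring syntax. Data collection and the sample size do not change.
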